### Participants

Eligible participants are adults aged ≥18 years with adult-onset audiometric HI, without significant cognitive impairments or neurological conditions. Participants are prescreened via telephone and in-person visits conducted by community workers and confirmed with some degree of HI through audiometric assessment by professional audiologists. The eligibility criteria are mentioned in Textbox 1.

Inclusion and exclusion criteria.
**Inclusion criteria**
Age (18 years or older): individuals aged 18 years at the time of recruitment are eligible for the trial. This age range meets the needs of this study by targeting adult-onset hearing impairment (HI). Besides, given that adult-onset HI is more prevalent in middle-aged and older adults, individuals who develop hearing loss after the age of 55 years are preferentially included.Residency: community-dwelling within the sites for the duration of the study.Audiometric hearing impairment: participants must have adult-onset audiometric HI with a 4-frequency (0.5, 1, 2, and 4 kHz) PTA hearing threshold ≥21 dB hearing level (HL) and ≤90 dB HL in a better hearing ear (ranging from mild, moderate, severe to profound hearing loss according to the World Health Organization (WHO) 2021 grades of hearing loss [32]). These grades of hearing loss indicate the level at which individuals are likely to benefit from the use of hearing aids or other amplified devices.No significant diagnosed or self-reported history of dementia or neurological impairments.Communication: Fluent in Mandarin or Cantonese with basic word recognition skills.Willing to participate, be randomized, and adhere to the protocol: Participants must be willing and able to consent to engage in the study, be willing to participate in the interventions, and commit to adhering to the study protocol until the end of the trial (24 months after the baseline survey).
**Exclusion criteria**
Profound, complete, or total hearing loss or deafness: pure tone audiometry (PTA) at 4 frequencies for better ear of >90 dB HL, who are suggested to face challenges in effectively participating in the intervention setting [33].Significant ongoing ear-related diseases, medical contraindications to the use of hearing aids, or permanent conductive HI.Recent use of hearing aids or other listening devices: to assess the net effect of hearing interventions, participants should not be receiving any treatment for the HI already.Previous dementia diagnosis and self-reported mental health problems: self-reported diagnoses of dementia or memory-related diseases, and those who required a proxy to provide informed consent and answer questions due to cognitive problems or other mental health issues are excluded.Unwillingness to wear hearing aids regularly.Visual impairment: participants who are unable to see well enough (even with correction) to read a brochure or watch an online video are excluded.Unable or unwilling to provide written informed consent.

### Sample Size Calculation and Recruitment

Sample size calculations are based on the expected effects of the hearing aid intervention on the primary outcome: an individual’s functioning in society measured by the World Health Organization Disability Assessment Schedule 2.0 (WHODAS 2.0), which was developed within the ICF conceptual framework [34]. We estimate that a sample size of 222 (111 participants in each group) provides 85% statistical power with a 5% significance level to detect a standardized effect size of 0.404 for the difference between the HAU group and the control group in the mean change from baseline in the functioning score at the 24-month follow-up [23]. Since there is little evidence evaluating the effects of HAU on social isolation using the Lubben Social Network Scale (LSNS), or the effectiveness of HHE on functioning and social isolation, we will assign the HHE group the same sample size as the HAU group and the control group. To account for a 20% drop-in (uptake of hearing aids in the control group) and dropout (discontinuation of HAU in the hearing intervention group) rate, a total of 435 individuals are included. This comprises 121 individuals in the HAU group, 158 in the HHE group, and 156 in the control group, respectively. Recruitment activities are conducted in communities and villages (n=8) from Guangzhou, Shanwei, Chaozhou, and other areas in Guangdong Province, China. The recruitment of participants commenced on September 1, 2022, and was completed on September 31, 2022. Oral informed consent is obtained through prescreening, and written informed consent is presented by the investigator to the participant before the hearing screening. Hearing screening and assessment will be undertaken by an audiologist following a standardized procedure (Table 1).

**Table 1 table1:** Schedule of enrollment, interventions, and assessments.

Time point				Study period																												
				Enrollment T_1_						Allocation T_0_					Postallocation T_1_							Postallocation T_2_						Close-out T_4_				
				–30 to –1 Day						Day 0					6 months							12 months						24 months				
				T^a^		T^b^		C^c^		T	T		C		T		T		C		T			T		C	T			T		C
Enrollment																																
Eligibility screen				✓		✓		✓																								
Informed consent				✓		✓		✓																								
Demographics				✓		✓		✓																								
Health history				✓		✓		✓																								
Visual status				✓		✓		✓																								
Allocation										✓	✓		✓																			
Interventions																																
Hearing aids provision										✓											✓						✓					
Hearing health education											✓						✓							✓						✓		
Assessments																																
Sociodemographics										✓	✓		✓														✓			✓		✓
Hearing outcomes																																
Pure-tone audiometry										✓	✓		✓																			
HHIA^d^ score										✓	✓		✓														✓			✓		✓
Self-reported hearing										✓	✓		✓														✓			✓		✓
IOI-HA^e^ score																											✓					
Hearing-related health literary										✓	✓		✓														✓			✓		✓
Communication ability											✓		✓														✓			✓		✓
SWB^f^ (primary outcome)																																
LSNS-6^g^ score										✓	✓		✓		✓												✓			✓		✓
WHODAS 2.0^h^ score										✓	✓		✓		✓												✓			✓		✓
ISE^i^ score										✓	✓		✓		✓												✓			✓		✓
SEAQ^j^ score										✓	✓		✓		✓												✓			✓		✓
Secondary outcomes																																
GSE^k^ score										✓	✓		✓														✓			✓		✓
PMS^l^ score										✓	✓		✓														✓			✓		✓
CD-RISC^m^ score										✓	✓		✓														✓			✓		✓
EQ-5D-5L score										✓	✓		✓														✓			✓		✓
SWLS^n^ score										✓	✓		✓														✓			✓		✓
Covariates										✓	✓		✓														✓			✓		✓
Lifestyle behaviors										✓	✓		✓														✓			✓		✓
Chronic diseases										✓	✓		✓														✓			✓		✓

^a^T: hearing aid intervention group.

^b^T: hearing health education intervention group.

^c^C: control group.

^d^HHIA: Hearing Handicap Inventory Screening Questionnaire for Adults.

^e^IOI-HA: International Outcome Inventory for Hearing Aids.

^f^SWB: social well-being.

^g^LSNS-6: Lubben Social Network Scale.

^h^WHODAS 2.0: World Health Organization Disability Assessment Schedule 2.0.

^i^ISE: Index of Social Engagement.

^j^SEAQ: Social Engagement and Activities Questionnaire.

^k^GSE: General Self-Efficacy Scale.

^l^PMS: Pearlin Mastery Scale.

^m^CD-RISC: Connor-Davidson Resilience Scale.

^n^SWLS: Satisfaction with Life Scale.

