### Study Design and Setting

A three-arm, single-blinded RCT with a 24-month follow-up period will be conducted. A total of 435 eligible participants were randomly assigned in a 1:1:1 ratio to a control group, a hearing aid use (HAU) group, or an HHE group. The HAU group will receive hearing aids and follow-up instructions. Due to budget constraints, the audiological rehabilitation intervention predominantly used hearing aids provided by the Audiology Department of the Guangdong Provincial Cultural Sports and Rehabilitation Assistive Devices Center for People with Disabilities (GPSRC), which is affiliated with the China Disabled Persons’ Federation (CDPF). Individuals diagnosed with disabling HI and classified as persons with hearing disability are eligible to apply for complimentary hearing aids and fitting services from the local CDPF departments. Since the number of adults with HI who were eligible for hearing-aid fitting was limited to one site at the time of the baseline survey and intervention, a total of 139 persons with disabled HI were randomly selected from 4 sites with similar socioeconomic and cultural conditions. The selection was based on the list provided by GPSRC, which maintains records of hearing-disabled persons in Guangdong Province. The HHE group will undergo both offline and online educational interventions, while no interventions are planned for the control group that is similar to a natural setting. A sample of 278 adults diagnosed with some degree of HI was randomly selected and assigned to the HHE group and control group from Hualong County in Guangzhou, Guangdong, based on its roster. For the HAU group, participants were prescribed hearing aids at baseline (T0) and received reinstruction on the use of hearing aids 12 months after T0. For the HHE group, participants were required to participate in an offline hearing education at T0, followed by an online educational intervention at 6 months after T0, and an offline information intervention at 12 months after T0. The primary outcomes are social isolation and functioning, assessed at baseline and 24 months.

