### Statistical Analysis

The intent-to-treat principle will be used during the impact analysis. The differences between the control and intervention groups in terms of primary and secondary outcomes will be evaluated through ANOVA and linear mixed-effects modeling. Multiple methods such as weighting, matching, and imputation will be used to handle the problem of missing data and sample attrition. In addition, a nonparametric bias-corrected case resampling bootstrap method, structural equation modeling, or interaction analysis will be used to further explore the buffering effect of psychosocial factors. Heterogeneity analysis will be applied to investigate whether the intervention effects are robust across subgroup samples, such as participants with different levels of objective hearing loss.

The cost-effectiveness analysis will be based on the costs of the HAU or HHE interventions and their effects on improving health-related quality of life, as measured by EQ-5D-5L. EQ-5D-5L is designed to measure the generic quality of life in terms of mobility, self-care, usual activities, pain or discomfort, and anxiety or depression [49]. Previous literature has used this multidimensional construct of quality of life to evaluate the effect of hearing interventions [50-53].

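### The 85% power for HAU versus control assumes independent participants, although on the protocol's own recruitment account these two arms come from different sites

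*Protocol article*

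**What the plan says.** Sample Size Calculation and Recruitment sizes one contrast only: "We estimate that a sample size of 222 (111 participants in each group) provides 85% statistical power with a 5% significance level". The target is "to detect a standardized effect size of 0.404 for the difference between the HAU group and the control group", measured as mean change in WHODAS 2.0 from baseline to 24 months. The section names no ICC, design effect or site term. It counts 8 communities and villages over the whole trial and does not split them by arm.

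Study Design and Setting gives the arms different sources. For HAU, "a total of 139 persons with disabled HI were randomly selected from 4 sites with similar socioeconomic and cultural conditions", using the provincial list of hearing-disabled persons. The other sample was "assigned to the HHE group and control group from Hualong County in Guangzhou, Guangdong, based on its roster". Limitations accepts that the interventions run at different sites and that geographical and selection bias may follow.

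Two statements point the other way. Study Design and Setting also describes 1:1:1 random assignment, and Randomization, Allocation, and Masking says that randomization is stratified by hearing impairment severity and field site.

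Under Statistical Analysis, differences between the groups "will be evaluated through ANOVA and linear mixed-effects modeling". The random effects are not named.

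**The concern.** If HAU participants live in one set of places and controls in another, the difference between the arms contains the difference between the places. The part of 24-month change that people in one community share (local services, social life, perhaps interviewers) does not average out as more people are added. A power calculation on independent people leaves this out, and a plain ANOVA divides by the number of people as if it were absent. At stake is the only stated power in the protocol, and the p-value of an ANOVA on the same contrast.

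This is a point about variance. It is distinct from systematic imbalance between the sources, and it would remain even if the arms had the same expected baseline. HHE and control come from one county, so it does not apply to that contrast in the same way.

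**Working it through.** **Inputs from the protocol.** Effect size 0.404, 5% level, 111 per arm, 85% power, 20% allowance, 8 communities and villages, and enrolled numbers of 121 (HAU) and 156 (control), all from Sample Size Calculation and Recruitment. The 4 HAU sites and one county for control come from Study Design and Setting.

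**Assumed, because not in the protocol.** The ICC of the change score is 0.005, 0.01, 0.02 or 0.05. The number of clusters is 4 v 4 (one possible split of the 8 communities) or 4 v 1 (Hualong as one site). Clusters within an arm are of equal size, the total SD is 1, and the between-site variance is the same in both arms.

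**1. Reproduce the stated figure.**
- n per arm = 2(1.960 + 1.036)² / 0.404² = 110.0, rounded up to 111 (two-sided). A one-sided test would need 89, so the plan is two-sided.
- SE = √(2/111) = 0.1342 and 0.404/0.1342 = 3.010. Power = Φ(3.010 − 1.960) = 85.3%, or 85.0% by the noncentral t.
- 111/0.80 = 138.75, rounded up to 139, and 222/0.80 = 277.5, rounded up to 278. These are the numbers in Study Design and Setting.

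The 20% allowance accounts for all the inflation, and nothing is left for clustering.

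**2. Let the arms share no site.** With k₁ and k₂ clusters,

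V = ICC(1/k₁ + 1/k₂) + (1 − ICC)(1/n₁ + 1/n₂), and V₀ = 1/n₁ + 1/n₂.

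Power = Φ(0.404/√V − 1.960). Type I error of a test that ignores site = 2[1 − Φ(1.960√(V₀/V))].

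Example, 4 v 4, ICC 0.01: V = 0.01 × 0.5 + 0.99 × 0.01802 = 0.02284, so V/V₀ = 1.27. Power = Φ(2.673 − 1.960) = 76.2%. Type I error = 2[1 − Φ(1.741)] = 8.2%.

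At 111 per arm with a normal reference:

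| ICC | 4 v 4: V/V₀ | power | naive type I | 4 v 1: V/V₀ | power | naive type I |
|---|---|---|---|---|---|---|
| 0 | 1.00 | 85.3% | 5.0% | 1.00 | 85.3% | 5.0% |
| 0.005 | 1.13 | 80.7% | 6.6% | 1.34 | 73.8% | 9.1% |
| 0.01 | 1.27 | 76.2% | 8.2% | 1.68 | 64.0% | 13.1% |
| 0.02 | 1.54 | 68.1% | 11.4% | 2.37 | 49.8% | 20.3% |
| 0.05 | 2.34 | 50.3% | 20.0% | 4.42 | 29.9% | 35.1% |

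The first term of V does not shrink with more participants. For 4 v 1, V tends to 1.25 × ICC, and 85% power needs V ≤ (0.404/2.996)² = 0.0182. Above an ICC of about 0.0182/1.25 = 0.0145, no number of participants reaches 85%.

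**3. Show the small-degrees-of-freedom penalty separately.** For 4 v 4, a test with 4 + 4 − 2 = 6 df has power 70.9% even at ICC 0, then 65.6%, 60.9%, 53.1% and 38.1% over the four ICCs. At ICC 0.005 the fall from 85.3% to 65.6% is therefore 14.4 points from the 6 df and 5.3 points from clustering.

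**4. Enrolled numbers, 121 v 156, no loss, normal reference.** Independent: 91.5%. For 4 v 4: 87.1%, 82.4%, 73.5% and 53.5%. For 4 v 1: 79.9%, 69.1%, 53.0% and 30.9%.

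**The case against.** Five things can fairly be said on the other side.

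- **Nesting is not certain.** The randomization section stratifies by field site. If the arms were randomized within site and the analysis accounted for site, this inflation would not arise. The protocol also does not say whether Hualong is one of the 4 HAU sites; Guangzhou, where Hualong lies, is among the recruitment areas. This stands as a reason to reconcile the sections first. Separate sources are still the more specific account, and Limitations agrees with it. Partial overlap would not remove the problem: if Hualong were one of 4 equal HAU sites, the multiplier of the ICC in an unadjusted comparison would be (1 − 1/4)² + 3 × (1/4)² = 0.75, between the 0.5 and 1.25 used above.
- **The mixed model could carry a site effect.** This stands. A reader might infer that all planned intervals are too narrow. The documents do not support that: the random effects may be set in a fuller plan, and the fault is shown for the plain ANOVA only.
- **The size is unknown.** This stands. No ICC or split of communities is given, and taking change from baseline removes stable differences in level between communities, so the relevant ICC may be small.
- **Enrolment gives slack.** This stands in part. With 121 and 156, 4 v 4 and no loss, power is still 87% at ICC 0.005. A reader might infer that 85% is lost at any positive ICC whatever the enrolment; that is true only at the stated 111 per arm. The surplus was also meant to cover drop-in and dropout.
- **Confounding is the larger problem.** Agreed. In Table 2, poor self-rated economic status is 80% in HAU and 25.32% in control, and mean age is 67.02 and 74.82 years. Wider intervals do not cure that.

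**Conclusion.** The concern holds in direction, not in a fixed size. The arithmetic behind 111 per arm is correct; the fault is the unstated assumption of independence beside a recruitment account that places HAU and control in different sites. If the arms share no site, any positive between-site correlation in 24-month change puts power at 111 per arm below 85% and makes a plain ANOVA of HAU against control anti-conservative. Under the assumed ICCs, the loss ranges from about 5 points (4 v 4, ICC 0.005) to about 55 points (4 v 1, ICC 0.05).

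A reader might take the 6-df figures of 66% down to 38% as the cost of clustering. They are not, because 71% is already the value at ICC 0. Nor do the documents show that the type I error is inflated to any particular level, since the ICC and the clusters per arm are assumptions.

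**What to change.** - **Reconcile** Study Design and Setting with Randomization, Allocation, and Masking: state whether HAU and control were randomized within any common site, and whether Hualong is one of the 4 HAU sites.
- **Sample Size Calculation and Recruitment:** give the number of sites or communities per arm, say that 85% assumes independent participants, and restate HAU-control power over a stated ICC range. Show any small-df penalty on its own line.
- **Statistical Analysis:** do not rest HAU-control on plain ANOVA. If each arm has several communities, use the mixed model already planned, with a community effect and small-sample degrees of freedom (Kenward-Roger or Satterthwaite), and report the estimated ICC.
- **If control is effectively one cluster,** state that the model cannot separate the hearing-aid effect from place, and report HAU-control with that limit. A random effect or cluster-robust standard error has no replication in that arm and would not repair the contrast.

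The cost is wording and one model term, with a less favourable power figure and wider intervals. Follow-up took place in September 2024, so the restated power cannot change the design. Trial Status says that the intervention effects were still unknown at this protocol version, so on that account the analysis choice could still be fixed without knowledge of them.

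### The 20% allowance is defined as crossover, which dilutes an intention-to-treat effect; the stated 435 (121/158/156) follows from no 20% rule and is not 1:1:1, so power for HAU versus control needs restating with its assumptions

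*Protocol article*

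**What the plan says.** All references are to the protocol article.

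- **Base calculation** (Sample Size Calculation and Recruitment): 222 people, 111 per group, is the size that, by the authors' estimate, "provides 85% statistical power with a 5% significance level to detect a standardized effect size of 0.404". The contrast is HAU against control in the change in WHODAS 2.0 score at 24 months. The HHE group is to be as large as each of the other two.
- **Allowance** (same section): "To account for a 20% drop-in (uptake of hearing aids in the control group) and dropout (discontinuation of HAU in the hearing intervention group"). The total of 435 is presented as the result.
- **Arm sizes** (same section): "This comprises 121 individuals in the HAU group, 158 in the HHE group, and 156 in the control group".
- **Allocation** (Study Design and Setting): "A total of 435 eligible participants were randomly assigned in a 1:1:1 ratio to a control group" and the two intervention groups. The same section has 139 people selected for HAU, and 278 selected and assigned to HHE or control.
- **Analysis** (Statistical Analysis): "The intent-to-treat principle will be used during the impact analysis".
- **Follow-up** (Trial Status): 435 recruited and assigned, 397 followed up at 24 months.

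**The concern.** Crossover and loss to follow-up call for different corrections. A lost participant reduces the number analysed, so n is divided by one minus the loss rate. A control who takes up a hearing aid, or an HAU participant who stops using one, still supplies an outcome and is analysed in the assigned arm. That shrinks the expected difference, so n must be divided by the square of one minus the crossover rate. The protocol describes the second situation, but its selection numbers fit the first rule.

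The stated total adds to the problem. It is offered as the product of the 20% allowance, yet it does not come from 111 per arm and 20% by either rule, and its arms are unequal although the text describes equal ones.

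What is at stake is how the HAU comparison is read. 85% is the only power figure given, and the Limitations section relies on the sample size having been set by standard methods. A null HAU result could be read as coming from a comparison with at least 85% power when, on the protocol's own crossover rate, it may have had noticeably less.

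**Working it through.** **Inputs.** Effect 0.404 SD, 5% significance (sidedness not stated; two-sided reproduces the figure), 85% power, 111 per group, 20% allowance, total 435, arms 121/158/156 (Sample Size Calculation and Recruitment); 139 and 278 selected (Study Design and Setting); 397 of 435 followed up (Trial Status).

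**1. The base figure reproduces.** n per arm = 2 x (1.960 + 1.036)^2 / 0.404^2 = 110.02, rounded up to 111. The t-test version gives 110.99. A one-sided test would give 89.

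**2. Where 139 and 278 come from.** 111/0.8 = 138.75, so 139; 222/0.8 = 277.5, so 278. Both match the rule for lost participants. The protocol does not state this step; it is inferred from the match.

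**3. 435 does not reproduce.** Three arms of 111 make 333.
- n/0.8: 3 x 139 = 417
- n x 1.2: 333 x 1.2 = 399.6, so 400; or 3 x 134 = 402 with rounding per arm
- Dilution rule: 3 x 172 to 3 x 174 = 516 to 522

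435 corresponds to an allowance of 1 - 333/435 = 23.4%.

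**4. What 20% crossover would need.** Take 20% as the combined rate, and assume those participants contribute no treatment contrast. The effect becomes 0.8 x 0.404 = 0.323. Solving directly gives 172 per arm; 111/0.64 = 173.4 gives 174. Call it about 173.

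**5. Power for HAU versus control at the realised sizes.** Power = Phi(d / SE - 1.960), with SE = sqrt(1/121 + 1/156) = 0.1211. For 397/435 = 91.3% retention, assumed equal by arm, d/SE is multiplied by sqrt(0.913) = 0.955.

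| Assumption about 0.404 | Effect used | Full follow-up | 91.3% retention |
|---|---|---|---|
| Full-adherence effect, 20% combined crossover | 0.323 | 2.668 - 1.960 = 0.708; 76% | 2.549 - 1.960 = 0.589; 72% |
| Already includes non-adherence | 0.404 | 3.335 - 1.960 = 1.375; 91.5% (t-test 91.4%) | 3.186 - 1.960 = 1.226; 89% |

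In the first row, 85% power would survive only with combined crossover of about 10% or less at full follow-up, or about 6% at 91.3% retention. The smaller HAU arm is not the cause: 139 against 139 would give 76.9% instead of 76.1% at full follow-up.

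**6. HHE versus control (158 and 156).** Detectable effect at 85% power = 2.996 x sqrt(1/158 + 1/156) = 2.996 x 0.1129 = 0.34 SD. At 91.3% retention it is 0.34/0.955, about 0.355 SD. The range is about 0.34 to 0.36 SD.

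**7. Counts.** 121/158/156 is neither 1:1:1 nor equal-sized. HHE plus control is 158 + 156 = 314, which is 36 more than the 278 said to have been selected and assigned to those two groups.

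**The case against.** The strongest reply is that the shortfall rests on what 0.404 represents. It comes from a cited hearing aid study, and the protocol does not say whether it is a full-adherence effect or an observed effect that already contains non-use. In the second case no dilution applies and power exceeds 85%. This stands, so the result has to be conditional. Against it, a further allowance for discontinuation and uptake would be redundant if 0.404 already contained them, so the protocol's own reasoning leans towards the first case without settling it.

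It is also fair that 85% is attached to 111 per group, where it is correct, and is never called intention-to-treat power for the enrolled sample. That link comes from the purpose of the allowance and the analysis principle. The use of the loss rule is likewise an inference, and it cannot explain 435.

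A reader might infer more than the document supports:
- **A separate 20% loss on top of crossover.** None is stated, and recorded loss is 38/435 = 8.7%.
- **20% crossover in each direction.** The wording could be read so, but the Control Group section cites 4.2% acquisition and 3% use of hearing aids as the natural setting for controls, which does not support 20% uptake there.
- **An undefined intention-to-treat set.** Trial Status gives 435 assigned, and Table 2 gives 121/158/156. Enrolling 121 from 139 selected is no contradiction in itself, because screening follows selection.
- **Missing participant accounting.** A flow diagram exists but is not shown here, so nothing can be concluded from its absence.

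**Conclusion.** The point holds in a limited form. The 20% is defined as crossover, and under intention to treat that calls for about 173 per arm, not 139. The stated 435 follows from no 20% rule. The realised arms contradict both the 1:1:1 ratio and the equal sizes described, and 314 in HHE plus control does not agree with 278.

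The size of any power deficit is conditional. It is about 76% (full follow-up) or 72% (397/435 retention) if three things are true: 0.404 is a full-adherence effect, crossover totals 20% across the two arms, and crossovers contribute no contrast. The 72% also assumes equal retention by arm, since the text shown gives no split of the 397. If 0.404 already includes non-adherence, power is about 89 to 91%. The documents therefore do not support a flat statement that the trial is underpowered. They do support saying that the power of the main HAU comparison does not follow from the plan as written.

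**What to change.** Change the text; do not enrol more participants.

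1. State the planned size as 139 per arm (417) and the realised size as 435 (121 HAU, 158 HHE, 156 control). Do not describe the realised allocation as 1:1:1 or equal, or present 435 as the result of the 20% allowance.
2. Reconcile the 278 selected and assigned with the 314 in HHE plus control.
3. Say whether 0.404 is a full-adherence effect or already includes non-adherence, and whether the 20% is the combined crossover rate. Then give the matching intention-to-treat power for HAU versus control: about 76% (full follow-up) and 72% (397/435, equal by arm) in the first case, or about 91% and 89% in the second.
4. State the detectable effect for HHE versus control, about 0.34 to 0.36 SD at 85% power.

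The cost is a few sentences, and possibly a less favourable power figure. Trial Status reports that intervention effects were still unknown at this protocol version; if that remains so, the restatement can be made before results are seen.
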